## Data collection and study safety

5

### Data collection

5.1

Demographics and preoperative conditions: gender, age, body mass index (BMI), American Society of Anesthesiologists (ASA) physical status classification, HAMA score, and comorbidities (hypertension, heart disease) will be recorded.

Intraoperative parameters: intraoperative fluid volume, blood loss, urine output, surgical duration, postoperative extubation time, and time of admission to the post-anesthesia care unit (PACU) will be documented.

### Study safety

5.2

Adverse events related and unrelated to taVNS will be recorded: skin erythema or rash, discomfort at the electrode site, dizziness, nausea, bradycardia, tinnitus, or hearing changes.

## Statistical analysis

6

Statistical analysis will be performed using SPSS 23.0 (IBM Corp, Armonk, NY, United States). The normality of continuous variables was assessed using the Kolmogorov–Smirnov (K–S) test. Normally distributed data were expressed as mean ± standard deviation (SD). One-way analysis of variance (ANOVA) was employed for multiple group comparisons, while the independent t-test was used for pairwise comparisons between groups. Paired *t*-test was applied for within-group comparisons. Non-normally distributed data were presented as median (interquartile range) and analyzed using nonparametric rank-sum tests. Categorical variables were compared using the chi-square test. A two-tailed *p*-value <0.05 was considered statistically significant.

The primary outcome measure will be analyzed using the intention-to-treat (ITT) principle. Missing data for the primary outcome were handled using multiple imputation by chained equations under the missing-at-random assumption. The interpolation model includes all the analytical variables as well as any auxiliary variables that may be related to the detachment. We generated imputed datasets using the mice package in R. The results from the imputed datasets were combined using Rubin’s rules.

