### Study design

2.1

This prospective randomized controlled trial will enroll 202 patients scheduled for radical mastectomy at our institution. Using a computer-generated randomization table, eligible participants will be allocated in a 1:1 ratio to either the treatment group (taVNS group) or the control group (sham stimulation group). The trial flow chart is shown in Figure 1. All participant characteristics and clinical outcomes will be documented using case report forms (CRFs). Data collection procedures are outlined in Table 1.

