#### Clinical symptom assessment indicators

4.2.1

(1)  Hamilton Anxiety Rating Scale (HAMA) (T0 to T6).(2)  Sleep quality score (T3 to T5): assessed using the Pittsburgh Sleep Quality Index (PSQI), with scores ranging from 0 to 21 (higher scores indicate poorer sleep quality).(3)  Incidence of postoperative delirium (T2 to T5): evaluated using the 3-Minute Diagnostic Interview for Confusion Assessment Method-Defined Delirium (CAM-3D).(4)  Pain score (T2 to T5): measured via the Numeric Rating Scale (NRS), ranging from 0 (no pain) to 10 (most severe pain).(5)  Frailty score (T3 to T5): assessed using the Fatigue, Resistance, Ambulation, Illnesses, and Loss of Weight (FRAIL), with scores ranging from 0 (most robust) to 5 (most frail).

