## Limitations

8

This study also has limitations. First, due to resource constraints, our assessment of anxiety relief was limited to the first three postoperative days. This timeframe is adequate for evaluating short-term therapeutic effects, but it may not fully capture long-term treatment outcomes. Second, the stringent inclusion criteria may restrict the generalizability of our findings to broader populations. Thirdly, the definition of a “subthreshold current” as the maximum intensity tolerated without eliciting sharp pain introduces substantial inter-patient variability that lacks standardization. This subjectivity represents a well-recognized challenge in non-invasive neuromodulation research. Therefore, real-world studies with extended follow-up and expanded patient populations will be conducted in the future.

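### The tests named for the repeated secondary outcomes fit the design poorly: ANOVA adds nothing with two arms, within-arm tests do not compare the arms, and no named method models the visits or adjusts for baseline

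*Protocol article*

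**What the plan says.** Section 2.1 (Study design) sets up two arms: "eligible participants will be allocated in a 1:1 ratio to either the treatment group (taVNS group) or the control group (sham stimulation group".

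Section 6 (Statistical analysis) then names its methods:

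- Continuous, normally distributed data: "One-way analysis of variance (ANOVA) was employed for multiple group comparisons, while the independent t-test was used for pairwise comparisons between groups".
- Change within an arm: a paired t-"test was applied for within-group comparisons".
- Skewed data: "Non-normally distributed data were presented as median (interquartile range) and analyzed using nonparametric rank-sum tests".
- Delirium and other categories: "Categorical variables were compared using the chi-square test".
- Threshold: a two-tailed p-"value <0.05 was considered statistically significant".

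The secondary outcomes in Sections 4.2.1 and 4.2.2 are all repeated. The first listed is "Hamilton Anxiety Rating Scale (HAMA) (T0 to T6"), which is seven ratings. HRV is recorded at six visits, NRS and CAM-3D at four, PSQI and FRAIL at three. Table 1 shows the same schedule.

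Section 8 (Limitations) says that "our assessment of anxiety relief was limited to the first three postoperative days", although Table 1 and Sections 4.1 and 4.2.1 schedule HAMA at day 30 (T6).

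**The concern.** The objection is to methods that the article states, not to detail that an analysis plan would supply later.

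- **ANOVA.** Two arms leave no set of several groups to compare. The phrase has a distinct object only if it means visits, and then the same women would be treated as independent groups.
- **Within-arm tests.** Patients enter with HAMA of at least 7 shortly before surgery (Section 2.3) and are rated again afterwards. Scores can fall in both arms through regression to the mean and the passing of the stressor. A significant fall in the taVNS arm is therefore not evidence that taVNS beat sham.
- **Visits and baseline.** None of the tests describes the between-arm difference over time, and none adjusts the HAMA or HRV comparison for its T0 value.
- **Number of tests.** Nothing limits which visits and indices may be called significant at 0.05, and nothing labels secondary results exploratory. HRV, on which the Discussion rests its mechanistic argument, has six indices.

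At stake is how far the secondary and HRV conclusions can be trusted. The primary conclusion is not affected.

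**Working it through.** **The plan's own figures.** The article gives no number of tests to reproduce. The only figure borrowed from it below is 91 patients per arm (Section 2.2). The unpooled formula returns it: (0.5×0.5 + 0.3×0.7) × (1.960 + 0.842)² / 0.2² = 90.3, rounded up to 91.

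**Step 1: count of between-arm tests, if every outcome is tested at every post-baseline visit.** Visits are from Table 1 and Sections 4.2.1 and 4.2.2.

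| Outcome | Post-baseline visits | Tests |
|---|---|---|
| HAMA | T1–T6 | 6 |
| PSQI | T3–T5 | 3 |
| Delirium (CAM-3D) | T2–T5 | 4, or 1 if analysed as any delirium |
| NRS | T2–T5 | 4 |
| FRAIL | T3–T5 | 3 |
| HRV (LF, HF, LF/HF, SDNN, SDANN, pNN50) | T1–T5 | 6 × 5 = 30 |
| **Total** | | **47 to 50** |

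Paired tests against T0 for HAMA and HRV would add up to 2 arms × (6 + 30) = 72.

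**Step 2: expected false positives when no effect exists.** 47 × 0.05 = 2.35 and 50 × 0.05 = 2.5. This expectation does not depend on correlation.

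**Step 3: chance of at least one false positive.** Under independence, 1 − 0.95^47 = 0.91 and 1 − 0.95^50 = 0.92. Repeated ratings and six indices from one recording are not independent, and the article gives no correlations, so a range is needed. Simulating 50 equally correlated test statistics gives:

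| Assumed correlation | Family-wise error |
|---|---|
| 0 | 92% |
| 0.3 | 80% |
| 0.5 | 62% |
| 0.7 | 40% |

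With correlation 0.6 within an outcome and 0.2 between outcomes it is 80%.

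**Step 4: how each named test behaves.** Simulated with 91 per arm, six visits and an assumed within-patient correlation of 0.5:

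- Between-arm t-test at one visit: 5.6% rejections under the null, so it holds its level.
- One-way ANOVA between two arms: F = t², the same test.
- One-way ANOVA across visits treated as independent groups: about 0.1% rejections with no time effect, against a nominal 5%. Patient-level variance stays in the error term but cancels between visits, so F averages about 1 − 0.5 = 0.5 where the test expects 1.

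**Step 5: after the change.** One comparison per outcome (HAMA, PSQI, NRS, FRAIL, delirium, six HRV indices) leaves 11: 11 × 0.05 = 0.55 expected false positives and a family-wise error of 1 − 0.95^11 = 43% under independence (about 30% at correlation 0.5). With the HRV indices labelled exploratory, 5 remain: 5 × 0.05 = 0.25 and 1 − 0.95^5 = 23% under independence.

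**The case against.** The strongest reply is that Section 6 is a generic list of tests in a condensed article, that longitudinal models and multiplicity rules for secondary outcomes usually belong in an analysis plan, and that the primary outcome is one comparison under intention to treat. Much of this stands. The article never says that each visit will be tested, so the count of 47 to 50 is conditional. The choice of multiplicity procedure or of a headline HRV index is a preference or a matter for the analysis plan. What the reply does not answer is that the article names ANOVA and within-arm tests, and that no method it names handles more than two visits jointly.

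Some stronger readings are tempting but not supported:

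- **All the tests ignore within-patient correlation.** A paired t-test uses the correlation of its two visits, and a t-test at one visit is valid though inefficient. Pooling visits as if independent would raise the error to about 30% in the same simulation, but the article does not propose that. ANOVA across visits errs in the conservative direction, so it would not generate chance findings.
- **The family-wise error is above 90%.** Only under independence.
- **One arm will often be significant and the other not.** With equal true improvement this happens with probability 2p(1 − p), which is 50% at power p = 0.5 and 32% at p = 0.8. No figure in the article supports such power. With 91 per arm it corresponds to a within-arm change of only about 0.2 to 0.3 SD; at 0.5 SD, power exceeds 99% and the probability is below 1%. Nor does the article say it would read such a pattern as efficacy.
- **The day-30 HAMA goes unused.** It is a listed secondary outcome. The defect is that Section 8 overlooks it.

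**Conclusion.** The point holds for the secondary outcomes. Three parts follow directly from the text: one-way ANOVA has no distinct between-arm use with two arms, within-arm paired tests do not estimate the taVNS-versus-sham effect, and no named method models the visit course or adjusts for the T0 HAMA and HRV values.

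The multiplicity figures (47 to 50 tests, about 2.5 expected false positives, family-wise error about 40% to 92%) rest on two assumptions: testing at every post-baseline visit, and correlations between 0 and 0.7. It would be wrong to infer that the primary result is compromised. The contradiction between Section 8 and the T6 rating is a separate matter of wording. Overall this is a worthwhile, inexpensive improvement and not a fatal flaw.

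**What to change.** Fix the following before unblinding:

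1. Delete one-way ANOVA from Section 6, and state that within-arm paired tests are descriptive and not evidence of efficacy.
2. Analyse each repeated continuous outcome with one mixed model containing arm, visit and arm-by-visit terms, allowing for correlation within patient, with the T0 value as covariate for HAMA and HRV. The other scales have no T0 rating in Table 1. Delirium analysed as any episode over T2–T5 can keep its chi-square test.
3. Report the between-arm difference with a confidence interval at one prespecified visit per outcome.
4. Label other visits and the HRV indices exploratory, without significance claims. Whether one HRV index is singled out, and whether a formal multiplicity procedure is added, can be left to the analysis plan.
5. Reconcile Section 8 with the day-30 HAMA in Table 1 and Sections 4.1 and 4.2.1.

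No new patients, visits or measurements are needed. The cost is modest programming, an amendment to the wording, and fewer nominally significant secondary results.

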### Inclusion criteria

2.3

Participants who meet all the following requirements will be enrolled:

(1)  Female patients aged 20–85 years.(2)  Patients scheduled for elective radical mastectomy.(3)  Preoperative patients with Hamilton Anxiety Rating Scale (HAMA) scores ≥7 measured before intervention.(4)  Patients with elementary school education or above, and normal communication, hearing, and comprehension abilities.(5)  Participants who voluntarily signed informed consent forms.(6)  Patients classified as American Society of Anesthesiologists (ASA) Physical Status I–III.

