### Primary outcome

4.1

The primary outcome is perioperative anxiety alleviation rate in patients subjected to either full-course taVNS or sham stimulation before the first intervention and after the last intervention. The anxiety alleviation rate will be calculated as follows: (baseline score − post-intervention score)/baseline score × 100%.

Perioperative anxiety will be assessed using the Hamilton Anxiety Rating Scale (HAMA), a 14-item scale with a total score ranging from 0 to 56. The severity of anxiety will be categorized as follows: total score <7: no anxiety; total score 7–13: mild anxiety; total score 14–20: moderate anxiety; total score >20: severe anxiety.

Patient anxiety will be assessed before (T0) and after (T1) the initial taVNS or sham stimulation. Further assessments occurr at 2 h post-surgery (T2), following the intervention on postoperative days 1 to 3 (T3–T5), and at 30 day after surgery (T6).

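### If the primary outcome is the continuous percentage reduction in HAMA, a K–S pre-test chooses its unadjusted test, so the effect measure and the quantity to be pooled are not fixed in advance, and some power is lost

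*Protocol article*

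**What the plan says.** Section 4.1 (Primary outcome) introduces a per-patient formula: "The anxiety alleviation rate will be calculated as follows", namely "baseline score − post-intervention score)/baseline score × 100" percent, taken from before the first session to after the last. HAMA is "a 14-item scale with a total score ranging from 0 to 56", and section 2.3 admits "Preoperative patients with Hamilton Anxiety Rating Scale (HAMA) scores ≥7 measured before intervention", so the denominator can be as small as 7.

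Section 6 (Statistical analysis) assigns no test to the primary outcome by name. Its general rule for continuous variables has three parts:
- "The normality of continuous variables was assessed using the Kolmogorov–Smirnov (K–S) test".
- If normal, "the independent t-test was used for pairwise comparisons between groups".
- If not, "Non-normally distributed data were presented as median (interquartile range) and analyzed using nonparametric rank-sum tests".

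Section 6 then analyses the primary outcome by intention to treat, with chained-equations imputation assuming data are missing at random. It closes: "The results from the imputed datasets were combined using" Rubin's rules. No ANCOVA, regression or mixed model appears anywhere in the article. T0 HAMA is recorded for every patient (Table 1, sections 2.3 and 5.1) but enters only as the denominator of the percentage.

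**The concern.** Each element of section 6 is familiar, but together they do not define one primary analysis. A t-test compares means and a rank-sum test compares distributions. Which of these the trial reports is settled only after the outcome data have been seen. With multiple imputation the gate can also give different answers in different completed datasets, which leaves no common quantity to combine.

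Rubin's rules need an estimate and its variance from each dataset. The only summary that section 6 names for the non-normal branch is a median with interquartile range.

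There is also a question of efficiency. Percentage change puts the baseline in the denominator and makes no other use of it. At stake are a clearly defined primary effect and some power, not the validity of the randomised comparison.

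**Working it through.** **1. The plan's own figure.** Section 2.2 uses 50% v 30%, power 0.80 and alpha 0.05 (taken as two-sided). With unpooled variance:

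n = (1.960 + 0.842)² × (0.5×0.5 + 0.3×0.7) / 0.2² = 90.26, rounded up to 91.

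For dropout, 91 × 1.1 = 100.1, rounded up to 101 (91/0.9 = 101.1). The stated 91 and 101 per group reproduce. They concern a binary response, so they say nothing about power for the continuous percentage. The article gives no SD, baseline mean or correlation for HAMA.

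**2. The scale.** A 2-point fall is 2/7 = 28.6% from a baseline of 7 and 2/21 = 9.5% from a baseline of 21. The outcome cannot exceed +100% but is open downward: 7 to 21 gives (7 − 21)/7 = −200%.

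**3. Pooling.** With M imputed datasets, estimates Qₘ and variances Uₘ, Rubin's rules give the pooled estimate as the mean of Qₘ, with total variance = mean(Uₘ) + (1 + 1/M) × between-dataset variance of Qₘ. The t-test branch supplies Q (a mean difference) and U. For the rank-sum branch, section 6 names neither.

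**4. Power, set A.** Assumed, not in the article: normal baseline with mean 16, SD 4 or 6, entry at 7 or above, scores rounded, 91 per arm, 2,000 trials per scenario. Additive effect: control falls 4 points on average, and the treated arm falls 0.4 SD more. Proportional effect: 70% of baseline retained v 60%. The gate uses a Lilliefors-type critical value. Power in %:

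| Scenario | Gated route, % change | t-test, % change | % change adjusted for T0 | ANCOVA of follow-up HAMA | ANCOVA minus gated |
|---|---|---|---|---|---|
| Additive, SD 4, r 0.3 | 71.35 | 68.80 | 77.30 | 80.05 | 8.70 |
| Additive, SD 4, r 0.5 | 82.80 | 82.90 | 83.80 | 86.90 | 4.10 |
| Additive, SD 4, r 0.7 | 95.05 | 95.50 | 95.60 | 96.10 | 1.05 |
| Additive, SD 6, r 0.3 | 71.60 | 70.10 | 74.70 | 78.95 | 7.35 |
| Additive, SD 6, r 0.5 | 82.25 | 80.00 | 81.45 | 85.80 | 3.55 |
| Additive, SD 6, r 0.7 | 94.55 | 94.65 | 94.45 | 96.45 | 1.90 |
| Proportional, SD 4 | 92.75 | 92.70 | 92.90 | 96.85 | 4.10 |
| Proportional, SD 6 | 62.50 | 60.05 | 59.90 | 73.70 | 11.20 |

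The loss against the gated route, which is what section 6 describes, is about 1–11 points. Against the ungated t-test the largest gap is 73.70 − 60.05 = 13.65.

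**5. Power, set B.** Assumed: baseline mean 10–15, SD 5, correlation 0.3–0.7, 91 per arm. ANCOVA of T5 HAMA was ahead of the t-test on percentage change in all 12 scenarios, by about 1–12 points.

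**6. Source of the loss.** In set B, adding T0 HAMA as a covariate to the percentage change moved power by only about −1 to +6 points. In set A the same step gave −0.20 to +8.50. Moving from the adjusted percentage to the follow-up score gave the larger share in six of the eight set A scenarios; the exceptions are the two at correlation 0.3. Most of the loss therefore comes from the percentage scale, with the missing covariate mattering more when correlation is low.

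**7. Type I error.** The gated route rejected in 4.4–5.5% of trials across six null scenarios in set A. The Monte Carlo standard error is √(0.05 × 0.95/2000) = 0.5 points, so this is consistent with 5%.

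**8. How often the gate picks the rank-sum test.** In set B, normality was rejected in about 20–98% of trials with the Lilliefors correction, and in about 0–32% (mostly under 7%) without it. Section 6 does not say which version applies.

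**The case against.** The strongest objection is to the premise. Section 6 names no test for the primary outcome, section 2.2 sizes the trial on response rates, and the abstract speaks of a remission rate. If a responder proportion is intended, the chi-square test applies and the gate is irrelevant. This stands, so the point is conditional. But the formula in section 4.1 contains no responder threshold, which makes the continuous rule the natural reading of the text.

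An unadjusted comparison in a 1:1 randomised trial is also unbiased, and ANCOVA is an efficiency gain. That stands too. An unseen analysis plan could supply the pooled quantity, but section 6 already states the gate, the tests and the pooling, and these do not fit together as stated.

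A reader might infer more than the article supports:
- **That a rank-sum analysis cannot be pooled.** A Mann–Whitney probability or a location shift, each with a standard error, can be. The plan simply names neither.
- **That a few low-baseline patients dominate the mean.** This was not shown. With a gamma baseline truncated at 7 (mean 10–15, SD 5), at most 0.6% of patients fell below −100%, about 1 in 182. There the t-test was within about 3 points of the rank-sum test or up to 7 better; in set A it was at most 4.4 points worse.
- **That the rank-sum branch would be common.** This depends on the K–S version and could be close to never.
- **That the pre-test inflates false positives.** It did not in the scenarios tried.
- **That missing baseline adjustment alone explains the power loss.** Most of it comes from the percentage scale.

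**Conclusion.** The point holds on the continuous reading of section 4.1. The primary test and effect measure are left to a normality pre-test, they could differ between imputed datasets, and the rank-sum branch has no stated estimate for Rubin's rules. These conclusions come from the text and need no simulation.

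The power cost is about 1–12 points against ANCOVA of the post-intervention score, shrinking to about 1–2 points at correlation 0.7 with an additive effect. ANCOVA was ahead in every scenario tried, but the size rests on assumed SDs, effects and correlations of 0.3–0.7, none of which the article gives. Type I error is not a concern here. This is a change that should be made, not a flaw that invalidates the trial.

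**What to change.** Remove the K–S gate for the primary outcome and prespecify one model:
- **Continuous primary outcome:** regress T5 HAMA on arm and T0 HAMA (ANCOVA with robust standard errors). Fit it in each imputed dataset, pool the adjusted mean difference and its 95% CI by Rubin's rules, and report percentage reduction descriptively.
- **Responder primary outcome, if that is what section 2.2 intends:** fit a logistic model with arm and T0 HAMA, report a standardised risk difference, and pool it in the same way.

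The cost is analysis wording only, since T0 HAMA is already collected on everyone. The downside is that the headline effect of the continuous analysis would be in HAMA points, not percent, which departs from the measure in section 4.1. Recruitment is stated to run from August 2025 to August 2026, so the change must be documented before unblinding.

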## Discussion

7

To the best of our knowledge, this study represents the first systematic evaluation of the clinical efficacy and safety of taVNS for perioperative anxiety within the framework of a randomized controlled clinical trial (RCT) in China. The findings are expected to facilitate more effective management of perioperative anxiety, thereby improving patient outcomes and guiding clinical decision-making.

The autonomic nervous system (ANS), comprising the sympathetic nervous system and parasympathetic/vagus nerve, serves as a profound homeostatic regulatory system and constitutes a core component of emotional states. It reflects both vulnerability and resilience to psychological and physical health challenges (13, 14). Several disease-specific studies have demonstrated a close association between autonomic activity and emotional states such as depression and anxiety (15). Thayer and Lane (16) proposed that sympathetic activity serves as a determinant of emotional states, with the classic autonomic efferent pattern during emotional responses characterized by increased sympathetic activity coupled with decreased parasympathetic activity. In contrast, Jarrett et al. (17) suggested that negative emotional states (e.g., anxiety and depression) are exclusively associated with reduced parasympathetic tone. Consequently, the precise mechanisms underlying perioperative anxiety remain unclear, though they may involve disruption of ANS homeostasis.

The auricular branch of the vagus nerve represents the sole cutaneous branch of the vagus nerve. According to modern anatomical theory, the auricle is richly innervated, with nerve fibers predominantly concentrated in the cymba conchae, cavum conchae, and triangular fossa. Notably, the auricular concha region contains the only cutaneous vagal afferent fibers in humans. Experimental studies employing horseradish peroxidase (HRP) retrograde tracing of sensory neurons have untangled a potential neural pathway between the vagus nerve in the auricular concha region and the sympathetic ganglia innervating visceral organs. Furthermore, HRP labeling experiments have demonstrated that stimulation of the auricular concha region transmits signals to the nucleus tractus solitarius and medulla oblongata in the brainstem (18).

To address the limitations of implantable vagus nerve stimulation (VNS), including high procedural complexity, frequent complications, and substantial costs, transcutaneous auricular VNS (taVNS) was developed as a noninvasive alternative. This approach maintains therapeutic efficacy while reducing both risks and expenses (19). In 2010, Europe approved a taVNS device for the treatment of epilepsy and depression. Current research on taVNS efficacy has been conducted across multiple domains, including psychiatric disorders (e.g., depression, anxiety disorders, post-traumatic stress disorder), neurological diseases (e.g., epilepsy, migraine, stroke rehabilitation), and cardiovascular conditions. Recent mechanistic studies on taVNS suggest that its effects are not merely mediated by short-term electrochemical actions resulting from localized nerve fiber stimulation. Instead, taVNS exerts long-term regulatory effects through the neuro-endocrine-immune network (20).

This study employed a rigorous methodological strategy to enhance the reliability and validity of the research outcomes. First, randomization and blinding procedures were implemented to minimize potential biases and confounding factors. Second, a comprehensive set of endpoints was selected, including the primary efficacy indicator (perioperative anxiety relief rate) and multidimensional secondary endpoints—such as the HAMA, PSQI, CAM-3D, NRS, FRAIL, and autonomic nervous system monitoring HRV—to holistically evaluate the therapeutic effects in breast cancer patients undergoing radical mastectomy with perioperative anxiety. Notably, the study protocol innovatively incorporated HRV as an objective assessment tool to comprehensively evaluate physiological changes before and after anxiety relief. HRV, an internationally recognized and widely utilized noninvasive indicator for autonomic nervous system monitoring, reflects the balance between sympathetic and parasympathetic nervous activity as well as the complex interactions between the brain and cardiovascular system by detecting subtle variations in successive heartbeats (21, 22). HRV accurately captures changes in autonomic nervous system (ANS) function and balance. Previous studies have demonstrated that breast cancer patients with preoperative anxiety exhibit lower HRV after anesthesia induction compared to non-anxious patients (23). Additionally, breast cancer patients with a history of mood disorders display reduced autonomic flexibility following stress exposure (24), suggesting that HRV may serve as a potential biomarker for assessing negative emotional states such as anxiety and depression in cancer patients.

This study addresses the clinical challenge of perioperative anxiety by selecting patients undergoing radical mastectomy for breast cancer to investigate the effects of taVNS on alleviating perioperative anxiety. The autonomic nervous function was monitored through HRV analysis to explore the underlying mechanisms. The findings may provide novel insights for developing postoperative rehabilitation strategies.

